### 8. STUDY DISCONTINUATION AND PARTICIPANT DISCONTINUATION/WITHDRAWAL

#### 8.1 DISCONTINUATION OF STUDY SITE OR STUDY

The Sponsor has the right to terminate the study at any time. Reasons for site discontinuation include:

- Conduct of the study at this site is not in accordance with the GCP guidelines
- Repeated failure to complete documentation (source documents or eCRFs) / quality of data
- Failure to obtain Informed Consent
- Failure to report Serious Adverse Events (SAEs) within 24 hours of knowledge
- Repeated protocol deviations
- Failure to enroll an adequate number of subjects

The Study Sponsor also reserves the right to discontinue the entire study. Reasons the entire study could be discontinued include, but are not limited to:

- SAEs or if special circumstances concerning the Aviva therapy or the company itself occur, making further treatment of subjects impossible

In the event of site or study discontinuation, the study investigator(s) will be informed of the reason for study termination. Study materials must be returned, disposed of or retained as directed by the Study Sponsor.

#### 8.2 PARTICIPANT DISCONTINUATION/WITHDRAWAL FROM THE STUDY

Each participant has the right to voluntarily withdraw from the study at any time. To do so, he/she may notify a member of the research team of their decision to withdraw during study assessments or may contact the study PI at the phone number(s) listed on the informed consent document. Participants may stop participation without notifying a member of the research team (e.g., cease interaction with the app). Participants may be withdrawn from the study by the PI if they are unable to be contacted (lost to follow-up), become incarcerated, or are determined to be adversely affected by the study procedures. Participants who withdraw early from the study will have their access to the app revoked.

In addition, the investigator may discontinue or withdraw a participant from the study at any time if the investigator considers it necessary for any other reason including, but not limited to:

- Ineligibility (either arising during the study or retrospectively having been overlooked at screening)
- Significant protocol deviation
- Significant non-compliance with protocol or study requirements
- An adverse Event (AE) which requires discontinuation or results in inability to continue to comply with study procedures
- Participant are unable to be contacted (lost to follow-up)
- Participant becomes incarcerated
- Participant is determined to be adversely affected by the study procedures

Per the FDA regulations, when a subject withdraws from a study, the data collected on the subject to the point of withdrawal remains part of the study dataset and may not be removed. However, (as described in the informed consent) the investigator may ask a subject who is withdrawing

whether the subject wishes to provide continued follow-up and further data collection subsequent to the withdrawal from the treatment portion of the study. Staff will make every effort to collect final study visit assessments prior to withdrawal. Withdrawn participants will not be replaced for this study. The reason for withdrawal will be recorded in the source documents and eCRF. If the participant is withdrawn due to an AE, the investigator will arrange for follow-up visits or telephone calls until the AE has resolved or stabilized.

## 9. SAFETY

### 9.1 SAFETY HYPOTHESIS

Aviva is safe for use by individuals with a previous history of suicidal ideation and attempts.

### 9.2 ADVERSE EVENTS

An AE is any untoward medical occurrence, unintended disease or injury, or any untoward clinical sign (including an abnormal laboratory finding) in subjects, users, or other persons, regardless of whether or not it is related to the investigational medical device.

- This definition includes adverse events related to the medical device of this investigation or comparator.
- This definition includes adverse events related to the procedures involved (any procedures in the clinical investigational plan)
- For adverse events involving “users or other persons”, this definition is restricted to adverse events related to the medical device of this investigation.

Adverse events are classified and tabulated by relationship to procedure or device, severity, and body system. Serious Adverse Events (SAEs), deaths and Unanticipated Adverse Device Effects (UADEs) will be listed separately.

The following should not be recorded as AEs:

- Pre-planned procedure unless the condition for which the procedure was planned has worsened from the first study-related activity after the subject has signed the informed consent form.
- Pre-existing conditions found as a result of screening procedures. These should be recorded as medical history/concomitant illness.

Adverse events are graded on a 3-point scale and reported as indicated on the eCRF. The intensity of an adverse experience is defined as follows:

- **Mild:** Discomfort noticed, but no disruption to daily activity
- **Moderate:** Discomfort sufficient to reduce or affect normal daily activity
- **Severe:** Inability to work or perform normal daily activity

Study Relationship: the relationship of an adverse event to participation in the study will be assessed by the investigator as follows:

- **Definitely Related:** Clear-cut temporal association and no other possible cause.
- **Probably Related:** Clear-cut temporal association and a potential alternative etiology is not apparent.
- **Possibly Related:** Temporal association is less clear and other etiologies are also possible.
- **Not Related:** There is no temporal association and/or evidence exists that the event is definitely related to another etiology

All adverse event reports are filed as required by IRB and FDA regulations. For all adverse events (whether device-related or not), all sections of the appropriate Adverse Event Form(s) must be completed. **In this study, all adverse events are collected starting from the time informed consent has been signed.**

AE data will be collected on an adverse reporting form at the follow up assessments. Research assessors will ask participants, "Have you had any physical or mental health problems since our last call?" If the participant responds "yes", research assessors will note the specific event, event start and end dates, event intensity (whether the event was associated with participation in the study, actions taken to resolve the event (e.g., hospitalization) and the outcome of those actions (e.g., resolved). All adverse events (AEs) will be coded using the standardized Medical Dictionary for Regulatory Activities (MedDRA) central coding dictionary, version 24.1 or greater.

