#### **3.2.3 Safety Objectives**

Another objective is to assess the safety of Aviva. The safety hypothesis is that Aviva is safe for use by individuals with a previous history of suicidal ideation and attempts. Thus, no adverse events are anticipated specific to the Aviva device. Device specific adverse events are not anticipated because a) of the software nature of the treatment and b) participants in both conditions will receive treatment as usual. The primary risk to the participant is ineffective

treatment, resulting in a worsening of existing symptoms. This study will assess anticipated and unanticipated adverse events in the Aviva and sham conditions and assess for device relatedness. The primary anticipated events, therefore, include increased suicidal ideation and suicide attempts. Similar to the prior research, results from the SASII will be coded to match the C-SSRS (Comtois et al., 2019; FDA, 2012), which is consistent with FDA guidance for tracking suicide as an adverse event. For details on adverse events reporting in clinical trial see section 9.0.

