### 9.4 EXPECTED ADVERSE EVENTS IN PARTICIPANTS

Primary anticipated events therefore include:

- increased suicidal ideation
- hospitalization
- death by suicide

Any study participation related adverse events are to be followed until there is evidence of resolution or permanent change.

The determination of whether an adverse event is classified as a SAE or UADE is based on the definitions below, taking into account the clinical judgment of the investigator.

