### 9.6 UNANTICIPATED ADVERSE DEVICE EFFECTS

An UADE is defined as any serious adverse effect on health or safety or any life-threatening problem or death caused by, or associated with, the device if that effect, problem or death was not previously identified in nature, severity or degree of incidence in the investigational plan; or any other unanticipated serious problem associated with the device that relates to the rights, safety or welfare of subjects.

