##### 9.7.2 Sponsor Safety Reporting Requirements

SAEs and UADEs will be reported to the FDA, in accordance with 21 CFR Part 812.

In the event of a UADE, Sponsor will immediately conduct an evaluation of a UADE, and report the results of such evaluation to FDA and to all reviewing IRB's and participating investigators within see above comment. The Sponsor first receives notice of the effect. Thereafter, the Sponsor shall submit such additional reports concerning the effect as FDA requests.

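### Adverse events are to be tabulated by relationship to device or procedure, but the only graded rating is of relationship to taking part in the study, which cannot be split into the two

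*Protocol*

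**What the plan says.** Section 9.2 of the protocol sets the reporting axis: "Adverse events are classified and tabulated by relationship to procedure or device, severity, and body system". Its definition of an adverse event likewise treats device (or comparator) and procedures as separate sources.

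The rating instruction in the same section reads: "the relationship of an adverse event to participation in the study will be assessed by the investigator as follows". Four grades follow, from definitely related to not related. For the follow-up calls, research assessors note "whether the event was associated with participation in the study". Sections 9.4, 9.5 and 9.7 also speak of relationship to study participation.

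Device causality appears elsewhere without a scale:
- Section 3.2.3 says the study will assess events in both arms for device relatedness.
- Section 9.9 requires the PI to assess causality and mentions a suspected causal link to the investigational product.
- Section 11.5 has the DSMB review suicide attempts for causality to the device.

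On anticipated events, section 3.2.3 states "Thus, no adverse events are anticipated specific to the Aviva device" and then "The primary anticipated events, therefore, include increased suicidal ideation and suicide attempts". Section 9.4 opens its own list with "Primary anticipated events therefore include" and names increased ideation, hospitalization and death by suicide. Under section 9.6, an effect is a UADE if, among other things, it "was not previously identified in nature, severity or degree of incidence in the investigational plan". The sponsor's reporting duty in section 9.7.2 contains the fragment "within see above comment. The Sponsor first receives notice of the effect".

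**The concern.** A table can only show what was rated. If sites follow section 9.2 literally, the database will hold one relatedness grade per event, given against everything the participant does in the trial: the app, the interviews and the telephone contacts. The table announced in the same section needs device and procedure kept apart.

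This matters because the trial is described as pivotal for safety as well as effectiveness (2.1.2) and has a device-safety hypothesis (9.1). Section 9.5 gives a telling case. A missed follow-up visit is handled as an SAE, and a grade for its relationship to taking part says nothing about the app. Nor can an analysis plan repair this, because it cannot tabulate an attribute that was never recorded. Re-rating causality long after the event is a poor substitute.

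**Working it through.** No planned figure depends on the main point, so the check sets the provisions side by side.

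**1. Needed against collected**

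| Provision | Section | Relationship to what | Scale | Events covered |
|---|---|---|---|---|
| Tabulation | 9.2 | Device or procedure | none of its own | all AEs |
| Investigator rating | 9.2 | Study participation | four grades | all AEs |
| Call item | 9.2 | Study participation | none stated | events reported on calls |
| Safety objective | 3.2.3 | Device | none stated | AEs in both arms |
| PI causality | 9.9 | Unspecified; product mentioned | none stated | all AEs |
| DSMB review | 11.5 | Device | none stated | suicide attempts only |

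Only one row has a graded scale, and it is not on the axis of the first row.

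**2. Can the collected rating supply the table?** Take any grade above not related, say possibly related to participation. It fits an event possibly due to the app and not to procedures, and equally one possibly due to procedures and not to the app. At least two patterns therefore share each of the three upper grades. Only not related carries over to both columns.

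**3. UADE status.** Section 9.6 asks whether the effect was caused by or associated with the device, and whether the plan had identified it. The first part meets the same gap, but section 9.4 lets the investigator apply the definition with clinical judgment, so a decision can be made. The second part looks to the whole investigational plan. Suicide attempts are named as anticipated in 3.2.3 and again in 11.5.

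**4. Anticipated-event lists**
- 3.2.3: increased ideation, suicide attempts.
- 9.3 (seen in earlier trials): suicidality, hospitalization, death by suicide.
- 9.4: increased ideation, hospitalization, death by suicide.

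The lists in 3.2.3 and 9.4 share one item, increased ideation. Both are introduced as non-exhaustive, so they differ without strictly contradicting each other.

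**5. Frequency of attempts.** Section 9.6 counts degree of incidence, so the plan's own frequencies matter.
- Section 11.5: as many as half of those enrolled over 104 weeks, 0.5 × 391 = 195.5.
- Section 11.1.3: 52 events in 391, 52/391 = 13.3%.

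The 52 assumes staggered entry. For a like-for-like comparison, take the Attachment C monthly hazards with all participants followed for 24 months: 195 × (1 − e^(−0.0115×24)) + 196 × (1 − e^(−0.0044×24)) = 47.0 + 19.6 ≈ 66.7, or 66.7/391 ≈ 17%. The 11.5 figure is 195.5/66.7 ≈ 2.9 times that.

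**The case against.** The best reply is that device causality is not missing. Sections 3.2.3, 9.9 and 11.5 all call for it. Section 9.2 requires the adverse event form to be completed in full whether or not an event is device-related, and that form is not available, so it may already have a device field. This stands in part: investigators are not barred from judging device causality. But none of these provisions defines grades, 11.5 is confined to suicide attempts, and the form would have to depart from the protocol's own instruction to supply the table.

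A second reply is that device safety in a randomized sham-controlled trial rests on comparing event rates between arms. Follow-up contacts are common to both arms, and section 9.9 provides for that comparison. This also stands. A reader might infer that the device-safety claim has no basis; the documents do not support that.

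A reader might also infer that UADEs cannot be classified, or that two sites would have to label the same suicide attempt differently. Section 9.6 refers to the whole plan, and attempts are named in 3.2.3 and 11.5, so an attempt could be called unidentified in nature only by ignoring those sections. Nor does 3.2.3 contradict itself: it expects no events specific to the device, and then names events expected from ineffective treatment. Timely review does not hang on the label either, since SAEs reach the sponsor within 24 hours (9.7.1) and safety events reach the DSMB within 5 days (9.9).

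**Conclusion.** The mismatch within section 9.2 is real and should be corrected: as written, the plan yields a participation rating from which the promised tabulation by device or procedure cannot be built. It touches the relatedness rating of every adverse event in both arms, but no efficacy analysis, error rate or between-arm safety comparison. The conclusion assumes that the form follows the protocol's wording; a form with a separate graded device item would reduce this to a text correction.

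The differing lists, the two attempt frequencies and the leftover editing remark in 9.7.2 are minor. The frequencies are not a strict contradiction, since 11.5 states an upper limit from historical data, but they leave no single benchmark for degree of incidence. The remark displaces the sponsor's time limit, though 9.7.2 already binds reporting to 21 CFR Part 812, so the duty itself is not lost.

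**What to change.** In section 9.2 and on the adverse event form, replace the single rating with two investigator ratings on the same four grades: relationship to the assigned app (Aviva or sham, rated blind) and relationship to study procedures. Word the follow-up call item to match. The cost is one additional form field and a line in site training, with no added visits.

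Make three wording repairs at the same time:
- Align the lists in 3.2.3, 9.3 and 9.4 so that suicide attempts are treated the same way throughout.
- Reconcile the frequency in 11.5 with the design's 52 events in 391. Do not put arm-specific rates in the list: blinded investigators cannot apply them, and the hoped-for Aviva rate is an efficacy assumption, not a safety benchmark.
- In 9.7.2, replace the leftover remark with the sponsor reporting limit under 21 CFR Part 812, which that section already invokes.

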### 9.3 RATIONALE FOR IDENTIFICATION OF ADVERSE CLINICAL EVENTS

The proposed study protocol is based on previous trials of BCBT/CT-SP. Anticipated adverse clinical events are therefore derived from these previous trials. The BCBT/CT-SP developers have observed the following adverse events in their studies:

- suicidality
- hospitalization
- death by suicide

### 9.4 EXPECTED ADVERSE EVENTS IN PARTICIPANTS

Primary anticipated events therefore include:

- increased suicidal ideation
- hospitalization
- death by suicide

Any study participation related adverse events are to be followed until there is evidence of resolution or permanent change.

The determination of whether an adverse event is classified as a SAE or UADE is based on the definitions below, taking into account the clinical judgment of the investigator.

### 9.5 SERIOUS ADVERSE EVENTS

A SAE is any untoward medical occurrence that:

- Results in death
- Is immediately life-threatening
- Results in disability or permanent damage
- Requires intervention to prevent permanent impairment or damage
- Requires participant hospitalization or prolongation of existing hospitalization
- Is a congenital anomaly/birth defect, or
- Is any other serious or important medical event

Given the high risk of suicide attempt in this study population a missed follow-up visit, for collecting assessment data, will be treated as an SAE.

Important medical events that may not result in death, be life-threatening, or require hospitalization may be considered serious when, based upon appropriate medical judgment, they may jeopardize the participants' ability to participate and may require medical or surgical intervention to prevent one of the outcomes listed in this definition.

Planned hospitalization for a pre-existing condition, or a procedure required by the protocol, without serious deterioration in health, is not considered a SAE.

A SAE may or may not be considered related to study participation.

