the high risk and ethical concerns when doing research on suicide, the site PIs will ensure these two monitoring components are followed: 1) the clinical/safety monitoring of individual participants; 2) review of study data to assure data accuracy and consistency. DSMB members will include individuals who have extensive experience in clinical trials and suicide prevention. Site PIs will monitor data to determine whether study participation is leading to increased risk of harm to subjects by comparing rates and types of harm events across treatment arms. The DSMB will guide our team in assessing the risk of potential liability and matters of safety monitoring. During interim looks at the data for safety, the sponsor will continue to be blinded to condition, as will the assessors. The data will be tabulated by a CRO and forwarded to a DSMB for adjudication. There will be standard operating procedures for the DSMB meetings. Safety events/SAEs are clearly defined elsewhere in the protocol, with stopping rules (see section 11.5 STOPPING RULES). Safety events and SAEs will be reported to the DSMB for review by the DSMB in a timely manner (i.e. within 5 days). The study personnel and sponsor will remain blinded until all enrolled participants have completed the 104 week follow-up. If the DSMB requires the study be stopped (either for SAEs or positive outcomes/benefit), the study will be unblinded and a decision will be communicated to the Sponsor. The sponsor will notify the FDA.

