#### **11.1.3 Justification of sample size-suicide attempts**

Power and sample size calculations were made in nQuery, Version 8.7.2. Initial sample size calculations for suicide attempts were based on Rudd et al. (2015). A total sample size of 391 (with 52 events) is required to achieve 90% power to detect a hazard ratio of 0.3826 (for survival rates of 0.9240 in the Aviva group [group 1] and 0.8124 in sham app group [group 2] at 18 months), using a one-sided log rank test with 2.5% significance level (i.e.,  $p = 0.025$ ) assuming that the survival rates are exponential and that the total study time is 104 weeks (24 months) with 52 weeks (12 months) accrual.

These results assume that the group sequential design has 3 interim sequential tests (4 total looks including final analysis). The O'Brien-Fleming spending function is used to determine the effectiveness test boundary. See Attachment C: Power Calculation and Group Sequential Design for Aviva Trial – Suicide Attempts (Mathematical Formulations) for full details of sample size calculations.

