#### **11.1.4 Group Sequential Design for Suicide Attempts**

Although the dropouts will not provide the clinical interview information at study end, it will be possible to review hospital records to obtain information regarding suicide attempts by participants (this will be confirmed during informed consent). We will randomize 196 participants to the (Aviva) treatment group and 195 participants to the active control (sham) group and expect to have suicide attempt data for 100% of these participants. We investigated several reasonable variations of the group sequential design and determined that the following is most reasonable. We will test at the 0.025 significance-level (one-sided). The group sequential design has 3 interim sequential tests (4 total looks including final analysis). The looks will occur when 60%, 75%, 90% and 100% of the expected events (i.e., suicide attempts) have occurred. The O'Brien-Fleming spending function is used to determine the effectiveness test boundary. The group sequential design boundaries (on a z scale) are presented in Attachment C.

The power of this GSD is 90%.

Survival analyses will be conducted using the log-rank test for the effectiveness of the intervention on the time to the first suicide attempt after randomization while controlling for censoring effects due to the differential length of follow-up or the completion of follow-up without a suicide attempt. Time to suicide attempt will be measured by calculating the total number of days from enrollment to the first suicide attempt. For participants without a suicide attempt, the total number of days since enrollment to the last assessment will be calculated.

While every effort will be made to track suicide attempts (SA), there may be some missing data. Consistent with standard statistical procedures, missing data are included in the time-to-event analysis as censored observations, with the censoring time at the last contact time with the patient (Friedman et al., 2015).

Estimates of participants making at least 1 subsequent suicide attempt before study end and reattempt-free probabilities at any time point will be derived by the Kaplan-Meier method. The

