**PROPRIETARY AND CONFIDENTIAL**

Oui Therapeutics, LLC | [name]

level to detect a hazard ratio of 0.3826 when the group 1 exponential hazard rate is 0.0115 (this gives a group 2 exponential hazard rate of 0.0044). Under these assumptions, the number of events will be 37 and 15 in group 1 and group 2 respectively. The maximum follow-up time for a subject is 24 time units (months) with an accrual period of 12 time units.

These results assume that the group sequential design has 3 interim sequential tests (4 total looks including final analysis). The O'Brien-Fleming spending function is used to determine the effectiveness test boundary. The O'Brien-Fleming spending function is used to determine the non-binding futility boundary.

The drift parameter for this design equals 3.4387. The drift parameter equals the square root of the maximum information level by the log hazard ratio. The ratio of this drift parameter to the drift parameter from the equivalent fixed term design represents the ratio of the sample sizes required for this GST design to that of its fixed term equivalent.

GST Boundaries (Z scale):

Upper effectiveness bounds: 2.6686, 2.3865, 2.1685, 2.0748

Futility bounds: 0.8347, 1.3133, 1.7538, 2.0748

**ATTACHMENT D***TITLE: Mathematical Formulations for Suicidal Ideation*

PASS 2020, v20.0.3 9/10/2020 2:59:16 PM 1

Two-Sample T-Tests Assuming Equal Variance

Numeric Results for an Equal-Variance T-Test \_\_\_\_\_

 $\delta = \mu_1 - \mu_2$ Hypotheses:  $H_0: \delta = 0$  vs.  $H_1: \delta \neq 0$ 

| Power   | N1  | N2  | N   | $\delta$ | $\sigma$ | Alpha |
|---------|-----|-----|-----|----------|----------|-------|
| 0.83582 | 70  | 70  | 140 | 3.8      | 7.6      | 0.050 |
| 0.88160 | 80  | 80  | 160 | 3.8      | 7.6      | 0.050 |
| 0.91559 | 90  | 90  | 180 | 3.8      | 7.6      | 0.050 |
| 0.94043 | 100 | 100 | 200 | 3.8      | 7.6      | 0.050 |

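### Section 9.5 classes every missed follow-up assessment visit as an SAE against its own definition, so pooled SAE counts by arm mix retention with medical harm

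*Protocol*

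**What the plan says.** Protocol section 9.5 opens its definition with "A SAE is any untoward medical occurrence that" and lists the usual seriousness criteria: death, immediate threat to life, hospitalization and so on. After the list it states, because of the population's suicide risk, that "a missed follow-up visit, for collecting assessment data, will be treated as an SAE".

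Other sections determine what happens to such a record:

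- Section 9.2: SAEs are listed separately from other adverse events.
- Section 9.7.1: SAEs go to the sponsor within 24 hours. Section 8.1 makes failure to do so a ground for closing a site.
- Section 9.9: "Safety events and SAEs will be reported to the DSMB for review by the DSMB in a timely manner (i.e. within 5 days". The same section has rates and types of harm compared across arms, and allows the DSMB to stop the study for SAEs.
- Section 11.3: all safety analyses use the safety set, by treatment actually received.

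Table 1 schedules eight phone contacts, W1 to W104, each with a window of plus or minus 3 days. Section 7.7 names seven follow-up visits and leaves out W1.

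**The concern.** A missed data-collection call is not a medical occurrence and meets none of the criteria listed above it. Section 9.5 does not say that the record is provisional, that it is downgraded once the participant is found well, or that it is kept apart from medical SAEs. No other section says so either.

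Followed literally, the SAE count in each arm is medical SAEs plus missed calls. If retention differs between arms, that total shows a difference in harm that does not exist. If retention is equal, the shared missed calls pull a real difference in harm toward no difference. Section 3.2.3 makes the assessment of adverse events in both arms a safety objective, so this total is one that will be read.

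**Working it through.** **Inputs.** N, events and target: "A total sample size of 391 (with 52 events) is required to achieve 90% power to detect a hazard ratio of 0.3826" (section 11.1.3). Allocation: "We will randomize 196 participants to the (Aviva) treatment group and 195 participants to the active control (sham) group" (section 11.1.4). Attachment C supplies the hazards, "when the group 1 exponential hazard rate is 0.0115 (this gives a group 2 exponential hazard rate of 0.0044", and the timing: "The maximum follow-up time for a subject is 24 time units (months) with an accrual period of 12 time units". Section 11.5 gives the upper-bound attempt figures: up to half of participants over 104 weeks, and 2.5 attempts on average for a patient who attempts within the first year of treatment. The missed-call rate and the rate of SAEs other than attempts are not given.

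**1. Reproduce the 52 events.** With uniform accrual over 12 months, follow-up runs from 12 to 24 months and P(event) = 1 − [exp(−12λ) − exp(−24λ)] / (12λ).

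- Sham, λ = 0.0115: P = 0.186, and 195 × 0.186 = 36.3.
- Aviva, λ = 0.0044: P = 0.076, and 196 × 0.076 = 14.9.
- The total is 51.2. Rounded up by arm this is 37 + 15 = 52, as stated.

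**2. Calls due on the same basis.** With 12 to 24 months of follow-up, everyone reaches W52, about half reach W78 and almost none reach W104.

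- Seven-visit schedule: 5 + 0.5 = 5.5 calls each, so 391 × 5.5 = 2,150.
- With W1: 6.5 calls each, so 391 × 6.5 = 2,542.

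With all participants followed to W104 the totals are 391 × 7 = 2,737 and 391 × 8 = 3,128. Expected first attempts are then 195 × (1 − exp(−24 × 0.0115)) + 196 × (1 − exp(−24 × 0.0044)) = 47.0 + 19.6 = 66.7.

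**3. Break-even missed rate** = attempts / calls due.

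| Basis | Attempts | Seven visits | With W1 |
|---|---|---|---|
| Sizing, 12 to 24 months | 52 | 52 / 2,150 = 2.4% | 52 / 2,542 = 2.0% |
| Sizing hazards, full 24 months | 66.7 | 2.4% | 2.1% |
| Half attempt, full 24 months | 0.5 × 391 = 195.5 | 7.1% | 6.3% |
| Half attempt, 2.5 attempts each | 195.5 × 2.5 = 489 | 17.9% | 15.6% |

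All four rows treat attempts as the only medical SAEs. Hospitalization without an attempt, which section 9.4 anticipates, would raise every break-even rate by an amount the protocol does not let one calculate.

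The only attrition figure in the protocol is the 20% dropout used for the ideation sizing in Attachment D. At one missed call per dropout it gives 0.20 × 391 = 78 records. This is illustrative only, since that figure was not set for missed calls.

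**4. A difference created by retention (assumed rates).** Suppose harm is equal, with 5% of calls missed on Aviva and 10% on sham, on the 5.5-call basis. Missed-call SAEs are 196 × 5.5 × 0.05 = 54 against 195 × 5.5 × 0.10 = 107.

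**5. A difference diluted by retention (assumed rate).** First attempts alone are 15/196 = 7.7% against 37/195 = 19.0%, a ratio of 0.40. Suppose 20% of each arm miss at least one call, independently of attempts. The share with any SAE, 1 − (1 − p)(1 − 0.20), is then 26.1% against 35.2%, a ratio of 0.74.

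**The case against.** The rule can be read as an escalation rule: the event is treated as an SAE so that someone acts on it quickly. Section 9.4 leaves SAE classification partly to the investigator's clinical judgment. Adverse events are MedDRA coded (section 9.2), and section 9.9 compares types of harm as well as rates, so a careful analyst could pick these records out. Table layouts usually belong in the SAP or the DSMB charter.

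Much of this stands as mitigation. It does not remove the point, because the classification is fixed in the protocol itself, has no exception, and nothing requires the separation.

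A reader might infer that the SAE comparison would mainly measure call retention. The documents do not support that. It needs a missed-call rate the protocol does not give, and it takes first attempts as the only SAEs. On the section 11.5 upper bounds, a 5% missed rate leaves missed calls in the minority. Setting 3,128 calls against 52 attempts also mixes two follow-up assumptions: the calls need everyone to reach W104, while the 52 events assume 12 to 24 months.

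A reader might also infer that missed calls could stop the trial. Section 9.9 does allow stopping for SAEs, but no SAE count threshold exists. The only numerical trigger, in stopping rule 3 of section 11.5, is more suicide attempts in the treatment arm, which pauses enrollment for DSMB review. Nor is a formal test of total SAEs planned, so loss of power is not the right measure of the harm.

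Finally, removing the SAE label outright would not be free. That label is what carries the 24-hour and 5-day reports; the contact procedures in sections 7.7 and 10 set no such reporting deadline.

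**Conclusion.** The point holds as an internal contradiction in section 9.5 that distorts a planned safety display. Pooled SAE counts, rates and comparisons by arm would combine missed visits with medical harm.

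The size depends on a rate the protocol does not state. Missed calls match the planned first attempts at about 2% to 2.4% missed on the sizing assumptions. They match the upper-bound attempt figures only at about 7% to 18% (seven visits, full follow-up), and at higher rates once other hospitalizations are counted. The arm comparisons in steps 4 and 5 are illustrations on assumed rates, not forecasts.

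The primary endpoint and the attempt-based enrollment pause are unaffected. The change should be made, but it does not threaten the trial's main conclusion.

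**What to change.** Reconcile the two statements in section 9.5:

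- Keep the present escalation of a missed visit exactly as it is, and state that the 24-hour sponsor report and the 5-day DSMB report still apply to it.
- Flag these records in their own eCRF category.
- Tabulate them by arm in a separate table for the DSMB and the final report.
- Exclude them from SAE counts, rates and between-arm SAE comparisons unless contact or record review finds an event that itself meets the section 9.5 definition. In that case the event found is counted.

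The cost is one eCRF category, one table and a short addition to section 9.5. The explicit statement on timelines is essential: without it, reclassifying these records could remove the reporting deadlines that now depend on the SAE label.
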